### Health care providers' evaluation

*Gynecologists and oncology nurses *in both arms will be asked their opinion about the implementation of SCP care or usual care. At the beginning of the trial and after 12 months, gynecologists and oncology nurses will be asked to fill in a short questionnaire containing questions about the type of information they provide, how satisfied they are with the information they provide, how much time they spend on their consultations on average, to what extent they expect the SCP care to have a positive effect on patients, and how motivated they are to use the SCP. In addition, at the end of patient inclusion after 12 months, all gynecologists and oncology nurses in the SCP arm are invited to participate in qualitative interviews on their opinion about (the implementation of) the SCP care.

*General practitioners *of patients in both arms will be asked to fill in a short questionnaire, containing questions about whether they received the SCP and whether they believe it has improved the communication between themselves and the gynecologist, and between themselves and their patient.

### Sample size

The initial patient inclusion will be completed in approximately one year. Each year, approximately 250 endometrial and 200 ovarian cancer survivors are diagnosed in the participating hospitals. Based on previous studies [31-34] 337 patients (75%) are minimally expected to participate in one year. Allowing for 10% attrition, this equates about 300 patients. Assuming an average practice size, the power will be 0.98 to detect a minimum effect size of 0.5, which is considered clinically significant [35]. In addition, separate analyses for endometrial and ovarian cancer survivors can be conducted: 150 patients are sufficient to detect a half standard deviation difference with a power of 0.83.

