### Design

A pragmatic, cluster randomized controlled clinical trial (RCT) will be conducted, in which 12 hospitals will be randomized to either 'usual care' or 'SCP care'. It will be a longitudinal study, including patients immediately after initial surgery and following them for 24 months. The trial has been registered on http://www.ClinicalTrials.gov (NCT01185626). The description of this design follows the CONSORT recommendations for reporting on trials (http://www.consort-statement.org) with the extensions for pragmatic [15] and cluster [16] randomized trials.

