### Statistical analysis

Analyses will be performed adhering to the intention-to-treat principle. Descriptive statistics will be used to summarize characteristics of both hospitals and patients. Characteristics of patients (i.e., age, type of cancer, stage, treatment, socio-economic status, marital status, educational level, employment status) and hospitals (i.e., number of endometrial and ovarian cancer patients, whether a hospital is a training hospital) will be compared at baseline between the intervention and usual care group, by regression analyses.

Linear regression models will be used to analyze continuous outcome variables, and logistic models for binary outcome variables. All analyses will be adjusted for hospital, baseline values of the outcome measure, and baseline variables which differ to a clinically significant extent between groups. Differential effects of SCP care by age, type of cancer and baseline levels of the outcomes of interest will be assessed for the outcome measures by adding terms for the interaction between age, educational level, personality, type of cancer and baseline levels and care arm to the regression models.

A multilevel modeling approach [36] will be applied to evaluate differences between the intervention group and the control group. This approach will be used to take into account the clustering at the hospital level [37]. All statistical tests will be two-sided and considered significant if *p*<0.05. Repeated measures analysis using generalized estimating equations will be conducted to account for the intra-patient dependency of the repeated measures [38]. Differences in effect of the SCP care and usual care at the different time points will also be investigated [38].

Missing outcome data will be assumed to be 'missing at random' (MAR), conditional on key predictors of 'missingness' (in particular baseline values of the outcome variables of interest, and care arm). Clinically meaningful differences will be determined with Norman's 'rule of thumb', whereby a difference of ≈0.5 *SD *indicates a threshold of discriminant change in health status scores of a chronic illness [35].

Routinely collected data from the population-based Eindhoven Cancer Registry (ECR) and ROGY on patient and tumor characteristics will allow for the comparison of respondents, non-respondents and patients with unverifiable addresses, using t-tests for continuous variables and Chi-square analyses for categorical variables.

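### The plan's own accrual figures give about 135 ovarian patients for analysis, not 150, so the subgroup power of 0.83 does not hold for them; 0.98 and 0.83 both need an ICC below about 0.01 and a large-sample test

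*Protocol article*

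**What the plan says.** All the power statements are in the Sample size section of the protocol article. Each year "approximately 250 endometrial and 200 ovarian cancer survivors are diagnosed in the participating hospitals". Of these, "337 patients (75%) are minimally expected to participate in one year", and then "Allowing for 10% attrition, this equates about 300 patients". For the whole trial, "Assuming an average practice size, the power will be 0.98 to detect a minimum effect size of 0.5". The section then says that the two tumour types can be analysed separately because "150 patients are sufficient to detect a half standard deviation difference with a power of 0.83".

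The Design section makes the hospital the unit of randomisation, with 12 hospitals in two arms. The Statistical analysis section uses a multilevel model for clustering by hospital, adjusts for the baseline value of each outcome, and says "All statistical tests will be two-sided and considered significant if *p*<0.05". The article gives no ICC, design effect, number of patients per hospital or degrees of freedom for the arm comparison.

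**The concern.** Two things look wrong. First, 150 is half of the 300 expected overall, but the paragraph splits accrual 250 to 200 between endometrial and ovarian cancer. The smaller group therefore falls below the size to which 0.83 is attached.

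Second, the power figures are high for a trial of 12 clusters. The primary outcomes are satisfaction with the information and care given by the hospital's own staff, and the Intervention versus usual care section lets delivery vary between providers. Some between-hospital variation is therefore plausible, and power in such a design depends heavily on it.

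At stake is how the results are read. If a separate ovarian analysis shows no difference, a reader who trusts 0.83 will give that result more weight than the planned numbers allow. The same applies, less sharply, to the main comparison if the ICC is not close to zero.

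**Working it through.** **Inputs from the article.** Effect 0.5 SD; two-sided alpha 0.05; 300 patients overall and 150 per tumour type; 250 endometrial and 200 ovarian patients a year; 75% participation; 10% attrition; 12 hospitals.

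**Inputs assumed.** 6 hospitals per arm and equal hospital sizes (the article states neither); ICC from 0 to 0.05; no gain from baseline adjustment unless stated.

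**Step 1: analysed patients.**
- Overall: 450 × 0.75 = 337.5 (the article prints 337); 337 × 0.9 = 303, the article's figure of about 300.
- Endometrial: 250 × 0.75 × 0.9 = 168.75, about 169.
- Ovarian: 200 × 0.75 × 0.9 = 135. The count is 150 only before attrition (200 × 0.75), whereas the 300 is after attrition.

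**Step 2: reproduce the stated powers.** With N patients in total, design effect DE = 1 + (N/12 − 1) × ICC and noncentrality λ = 0.5 × √(N / (4 × DE)). Normal-test power is approximately Φ(λ − 1.96).
- No clustering (DE = 1): N = 300 gives λ = 4.33 and power 0.991; N = 150 gives λ = 3.06 and power 0.865. Neither matches to two decimals.
- ICC 0.008: N = 300 gives DE = 1 + 24 × 0.008 = 1.192, λ = 3.97, power 0.978. N = 150 gives DE = 1 + 11.5 × 0.008 = 1.092, λ = 2.93, power 0.834.
- ICC 0.009: 0.975 and 0.830.

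Solved separately, 0.98 needs an ICC of about 0.007 and 0.83 needs about 0.009. One value of about 0.008 to 0.009 matches both to rounding, so the figures look like a cluster calculation with a very small ICC and a normal test.

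**Step 3: the ovarian group on that same basis.** N = 135 gives 0.801 at ICC 0.007, 0.797 at 0.008 and 0.794 at 0.009, that is 0.79 to 0.80. With no clustering at all it gives 0.828, but 150 patients would then give 0.865, so the stated pair cannot have come from ICC = 0.

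**Step 4: allow for the number of hospitals.** The arm comparison is between 6 and 6 hospitals, so it has 12 − 2 = 10 degrees of freedom. Keep λ as above and use a noncentral t on 10 df (critical value 2.228). Power is shown as normal test / t on 10 df:

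| Assumed ICC | N = 300 | N = 169 | N = 150 | N = 135 |
|---|---|---|---|---|
| 0 | 0.99 / 0.97 | 0.90 / 0.83 | 0.86 / 0.79 | 0.83 / 0.74 |
| 0.01 | 0.97 / 0.94 | 0.86 / 0.79 | 0.83 / 0.74 | 0.79 / 0.70 |
| 0.02 | 0.95 / 0.89 | 0.82 / 0.74 | 0.79 / 0.70 | 0.75 / 0.67 |
| 0.05 | 0.83 / 0.75 | 0.71 / 0.63 | 0.68 / 0.60 | 0.66 / 0.57 |

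The Randomization section stratifies on annual patient numbers, so hospitals differ in size. With an assumed coefficient of variation of 0.5, the 10-df figures for 300 patients fall to 0.93, 0.87 and 0.69 at ICCs of 0.01, 0.02 and 0.05.

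**Step 5: credit for baseline adjustment.** Multiply the variance by 1 − r², where r is the correlation between baseline and follow-up (not in the article). With r = 0.5 on 10 df, power for 300, 150 and 135 patients is 0.98, 0.85 and 0.82 at ICC 0.01, and 0.86, 0.72 and 0.69 at ICC 0.05. With r = 0.3, 150 patients reach 0.82 even at ICC 0.

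**The case against.** The strongest reply is that the power figures reproduce. A single small ICC yields both, and a condensed article may leave that ICC to the full protocol. This stands: a reader might infer that clustering was ignored, or that the trial cannot deliver 0.98, and the article supports neither. The ICCs of 0.02 and 0.05 are assumptions that show sensitivity, not error.

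A reader might also infer from the 10-df ceiling of 0.79 that 0.83 is out of reach for 150 patients at every ICC. That holds only for an unadjusted comparison. The Statistical analysis section plans adjustment for baseline, and step 5 shows that r = 0.5 takes 150 patients to 0.85 at ICC 0.01. The article also names no reference distribution, so 10 df is a sensible standard for so few clusters rather than a stated feature of the plan. For 300 patients at ICC 0, the 10-df figure of 0.973 is trivially below 0.98.

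Nor does the article show that the ovarian group will fail to reach 150. The 75% is called a minimum and the accrual period is approximate. Participation of about 83% (150 / (200 × 0.9)), or about 13 months of accrual (150 / (135/12) = 13.3), would suffice. The text also does not literally promise 150 in each group, and the endometrial group exceeds it.

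What survives is that separate analyses of both tumour types are justified by 150 patients, while the same paragraph's figures give 135 for one of them. An unprinted ICC does not explain that.

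**Conclusion.** The subgroup statement is wrong as written for ovarian cancer. At the stated minimum participation and stated attrition, about 135 ovarian patients are expected, 15 fewer than the 150 behind the 0.83. On the plan's apparent method their power is 0.79 to 0.80, a shortfall of 3 to 4 percentage points. The expected count needs no outside assumption; the power figure rests on the ICC of about 0.007 to 0.009 recovered from the stated powers.

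The wider point is conditional. Without baseline credit, 0.98 and 0.83 are reproduced only with an ICC below about 0.01 and a large-sample test. On 10 df, 300 patients give 0.94 to 0.75 for assumed ICCs of 0.01 to 0.05. Those figures rest on 6 hospitals per arm, equal sizes and no baseline credit. Unequal sizes would lower them and baseline adjustment would raise them, though at ICC 0.05 even r = 0.5 leaves 0.86 for 300 patients and 0.69 for 135.

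**What to change.** Reword the Sample size section; no extra enrolment or change of design is needed.

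- Replace the 150-patient justification with the expected numbers by tumour type, about 169 endometrial and 135 ovarian, and drop 0.83 for the ovarian group.
- State the ICC, the degrees of freedom and any baseline correlation behind the power figures.
- Restate power for 0.5 SD over an ICC range labelled as assumed. For ICC 0.01 to 0.05 on 10 df without baseline credit, this is 0.94 to 0.75 for 300 patients, 0.79 to 0.63 for 169 and 0.70 to 0.57 for 135. If baseline adjustment is to be credited, give the assumed correlation and show both sets.

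The cost is a few sentences and less favourable power figures.

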### Statistical analysis

Analyses will be performed adhering to the intention-to-treat principle. Descriptive statistics will be used to summarize characteristics of both hospitals and patients. Characteristics of patients (i.e., age, type of cancer, stage, treatment, socio-economic status, marital status, educational level, employment status) and hospitals (i.e., number of endometrial and ovarian cancer patients, whether a hospital is a training hospital) will be compared at baseline between the intervention and usual care group, by regression analyses.

Linear regression models will be used to analyze continuous outcome variables, and logistic models for binary outcome variables. All analyses will be adjusted for hospital, baseline values of the outcome measure, and baseline variables which differ to a clinically significant extent between groups. Differential effects of SCP care by age, type of cancer and baseline levels of the outcomes of interest will be assessed for the outcome measures by adding terms for the interaction between age, educational level, personality, type of cancer and baseline levels and care arm to the regression models.

A multilevel modeling approach [36] will be applied to evaluate differences between the intervention group and the control group. This approach will be used to take into account the clustering at the hospital level [37]. All statistical tests will be two-sided and considered significant if *p*<0.05. Repeated measures analysis using generalized estimating equations will be conducted to account for the intra-patient dependency of the repeated measures [38]. Differences in effect of the SCP care and usual care at the different time points will also be investigated [38].

Missing outcome data will be assumed to be 'missing at random' (MAR), conditional on key predictors of 'missingness' (in particular baseline values of the outcome variables of interest, and care arm). Clinically meaningful differences will be determined with Norman's 'rule of thumb', whereby a difference of ≈0.5 *SD *indicates a threshold of discriminant change in health status scores of a chronic illness [35].

Routinely collected data from the population-based Eindhoven Cancer Registry (ECR) and ROGY on patient and tumor characteristics will allow for the comparison of respondents, non-respondents and patients with unverifiable addresses, using t-tests for continuous variables and Chi-square analyses for categorical variables.

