### Randomization

Hospitals have been pre-randomized whereby patients from a certain hospital will receive either usual care and information provision or an SCP. With this so-called pre-randomization, the conventional sequence of obtaining informed consent followed by randomization is reversed [18]. Pre-randomization is justified if valid evaluation of the effects of an intervention is impossible using a conventional randomized design, for example if knowledge of the intervention may lead to non-compliance or drop-out in the control group, or when the intervention is an educational program [18]. Pre-randomization at hospital level eliminates the problem posed by randomization at patient level in which health care providers from a hospital have to provide both types of care. By having to switch between usual care and SCP care for each patient, the health care provider could (unconsciously) influence the usual care group with that of the SCP approach by giving a patient randomized to usual care more information than was intended for usual care. Also, if usual care patients learn from other patients that they are given an SCP, it is possible that they will become dissatisfied with their usual care, even if the (dis)advantages are not well studied. This would bias the results of the study. To prevent imbalance between the treatment groups, stratified randomization was performed according to whether a hospital has a Gynecologic Oncology Center, and the annual number of endometrial and ovarian cancer patients, allowing for an even distribution of the intervention through the different participating centers.

Randomization to either usual care or SCP care at hospital level was performed with a table of random numbers by a researcher not involved in the study and blind to the identity of the hospitals. Because the health care providers administering the intervention have to know whether they have to provide either usual care or SCP care, it was not possible for them to be blinded to the group assignment. The participants on the other hand are unaware of the group assignment, as they are under the assumption that the hospital is providing usual care.

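### Covariates are chosen by observed baseline imbalance, and the two stratification factors of the randomisation are not planned covariates; the cost is precision and pre-specification, not inflated type I error

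*Protocol article*

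**What the plan says.** All from the protocol article.

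- Randomization: "stratified randomization was performed according to whether a hospital has a Gynecologic Oncology Center, and the annual number of endometrial and ovarian cancer patients". There are two factors, both at hospital level.
- Statistical analysis, the adjustment rule: "All analyses will be adjusted for hospital, baseline values of the outcome measure, and baseline variables which differ to a clinically significant extent between groups". The part at issue is the last one, "baseline variables which differ to a clinically significant extent between groups".
- Statistical analysis, how imbalance is looked for: patient and hospital characteristics "will be compared at baseline between the intervention and usual care group, by regression analyses". The hospital characteristics named are "hospitals (i.e., number of endometrial and ovarian cancer patients, whether a hospital is a training hospital"). Annual volume is therefore screened, and so is training status, which was not a stratification factor. Gynecologic Oncology Center status is not named.
- Statistical analysis, clustering: a multilevel model is planned, and "This approach will be used to take into account the clustering at the hospital level".
- Design: "12 hospitals will be randomized to either 'usual care' or 'SCP care". The split between arms is not given.

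**The concern.** The rule has two weaknesses.

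First, part of the covariate set is settled by looking at the arms at baseline. Under randomisation such differences are chance, and their size says nothing about whether a variable predicts satisfaction with information or care. What counts as a clinically significant difference in, say, marital status or treatment is not defined. Two analysts could reach different models, and so different adjusted effects, from the same data.

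Second, the rule works against the design. Stratification is meant to make center status and volume similar between arms, so an imbalance rule will tend to leave them out. If they predict the outcome, the variance they explain stays in the between-hospital error although the allocation has largely removed it from the treatment comparison. The reported standard error is then larger than the true one.

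At stake are precision, some power, and an adjusted estimate that was fixed in advance.

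**Working it through.** **Inputs.** From the article: 12 hospitals, about 300 analysable patients (so 300/12 = 25 per hospital), effect 0.5 SD, two-sided 5% test. Assumed, because the article does not give them: 6 hospitals per arm, the ICC, and the share of between-hospital variance that the strata explain.

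**The plan's own power.** With N patients in two equal arms, power = Φ(0.5/√(4·DE/N) − 1.96), where DE = 1 + (N/12 − 1)·ICC.
- N = 300: 0.991 with ICC 0. The stated 0.98 is reached at ICC about 0.007 (DE = 1 + 24 × 0.007 = 1.168).
- N = 150: 0.865 with ICC 0. The stated 0.83 is reached at ICC about 0.009.

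The stated power therefore fits an ICC of about 0.007 to 0.009. The checks below use 0.007, with 0.02 and 0.05 as larger assumed values.

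**Omitting the strata.** With total variance 1, a hospital mean has variance V = ICC + (1 − ICC)/25. If the strata explain half of the between-hospital part, this becomes V* = ICC/2 + (1 − ICC)/25.
- SE ratio = √(V/V*).
- Actual size of the 5% test = 2·P(t₁₀ > 2.228 × ratio).
- Power comes from the noncentral t with noncentrality 0.5/√(V/3) on 10 df (strata out), or 0.5/√(V*/3) on 8 df (strata in).

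| ICC | V | V* | SE ratio | Size | Power, strata out | Power, strata in |
|---|---|---|---|---|---|---|
| 0.007 | 0.0467 | 0.0432 | 1.040 | 0.043 | 0.949 | 0.953 |
| 0.02 | 0.0592 | 0.0492 | 1.097 | 0.035 | 0.893 | 0.926 |
| 0.05 | 0.0880 | 0.0630 | 1.182 | 0.025 | 0.749 | 0.855 |

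The strata-out power is the ordinary formula and slightly understates that analysis, because stratified allocation also makes the estimate itself less variable. Using noncentrality 0.5/√(V*/3) with critical value 2.228 × ratio gives about 0.955 at ICC 0.007, against 0.953 with the strata in: no gain. Simulation of stratified allocation (2 center hospitals, 4 high-volume and 6 low-volume hospitals, assumed) shows that the gain is real at larger ICCs:
- ICC 0.02: 0.899 to 0.905 if the strata explain 30%, and 0.901 to 0.933 if 60%.
- ICC 0.05: 0.747 to 0.795 if 30%, and 0.758 to 0.883 if 60%.

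**If the strata explain nothing.** Going from 10 to 8 df raises the critical value from 2.228 to 2.306. At ICC 0.007 power falls from 0.949 to 0.937.

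**Selecting on imbalance.** Take eight independent variables, each with ICC 0.03. The SE of an arm difference is √((0.03 + 0.97/25)/3) = 0.151 SD, so P(|difference| > 0.2 SD) = 0.187. The chance that at least one is flagged is 1 − 0.813⁸ = 0.81. With ICC 0 it is 0.50. With a 0.5 SD threshold it is below 0.01. The model thus turns on a threshold that the article does not give.

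A simulation with outcome ICC 0.03, covariate ICC 0.05 and eight prognostic covariates compared imbalance selection with a fixed list:

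| Threshold | Coefficient | Size, selected | Size, fixed list | 95% CI width, selected | 95% CI width, fixed list |
|---|---|---|---|---|---|
| 0.2 SD | 0.3 | 0.027 | 0.050 | 0.85 SD | 0.67 SD |
| 0.2 SD | 0.15 | 0.045 | 0.051 | 0.71 SD | 0.67 SD |

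At a 0.5 SD threshold almost nothing is selected (on average 0.03 variables), and the analysis is in effect unadjusted for them.

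**The case against.** **The harm is small at the ICC that the plan implies.** This stands. At ICC 0.007, with half the variance explained, the interval narrows by only 0.5% once the lost degrees of freedom are paid for. If the strata explain 30%, the adjusted interval is 1.1% wider. The planned adjustment for the baseline outcome may also remove some between-hospital variance already.

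**A reader might infer that inference is invalid or that false positives rise.** The checks do not support that. Apart from simulation noise around 0.05, size is at or below nominal throughout.

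**A reader might infer that people who know the arms judge the imbalance.** The Randomization section says only that care providers could not be blinded. The article does not say who analyses the data or what they know.

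**A reader might say that neither stratification factor can enter the model.** That is too strong. Volume is a screened characteristic and could enter; only center status is absent from the list.

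**The candidates are named and the criterion is clinical, not a p-value.** True, and this limits the freedom. But the only numerical yardstick in that section, about 0.5 SD, is stated for health status scores and has no clear meaning for categorical characteristics.

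**An article may leave the full covariate list to an analysis plan.** True of an omission. Here the article states a rule for all analyses, and a later fixed list would contradict it.

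**Adjusting for hospital already covers the strata.** It does not. Fixed hospital effects would absorb both factors but would also be confounded with arm, because whole hospitals are randomised. A random intercept does not adjust for them.

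**Conclusion.** The point holds as a poor rule stated in the article, with modest and conditional consequences. The imbalance clause should go whatever the ICC, because it chooses covariates by a criterion unrelated to prognosis, without a threshold, after baseline data are seen.

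The omission of the stratification factors matters only so far as they are prognostic and hospitals differ. Under the half-explained assumption the standard error is overstated by 4% to 18% over ICC 0.007 to 0.05. The power gain from including them runs from nil to about 0.1 at most. If the factors explain nothing, including them costs about 0.01 in power at ICC 0.007. The direction is conservative throughout. These sizes rest on 6 hospitals per arm, 25 patients in each, and ICCs and prognostic shares that the article does not give.

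The pre-specified adjustment for the baseline outcome is sound and should stay.

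**What to change.** Replace the imbalance clause with a short list fixed in advance for every model:

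- the baseline value of the outcome (already planned);
- Gynecologic Oncology Center status and annual patient volume, with volume coded as it was for the stratification;
- age, stage and tumour type, omitting tumour type in the separate endometrial and ovarian analyses described under Sample size, where it is constant.

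State that hospital enters as a random effect. Present the baseline comparison of arms descriptively, and do not use it to choose covariates.

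The cost is a change of wording and 2 of the 10 between-hospital degrees of freedom. With only 12 hospitals the list of hospital-level terms should stay at these two. Before the analysis, check from the hospital list alone whether center status and volume are so closely related that both cannot be estimated, and state in advance what will be done if so. The patient variables are already among the planned measures, and the two hospital factors are known from the randomisation.

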## Methods/Design

### Objectives and hypotheses

The aim of the proposed study is to assess the impact of SCP care on patient and health care provider reported outcomes in routine clinical practice. Primary outcomes include patients' satisfaction with information provision, and satisfaction with care. Secondary outcomes include patients' health-related quality of life, illness perception, health care use, prevalence, course and referral rate of patients with psychosocial distress, and health care providers' evaluation of the (implementation of the) SCP.

It is hypothesized that patients who receive SCP care report better satisfaction with information provision, better satisfaction with care, and more adequate illness perception than those who receive usual care. It is furthermore hypothesized that patients who receive SCP care will report a higher health care use compared to those receiving usual care [14]. In addition, it is expected that patients who receive the SCP will report less anxiety, less depression or psychosocial stress and better HRQoL. However, there may be subgroups (dependent on patient characteristics, such as age, education, and personality) that will be influenced in a negative way when receiving more information than they can handle. Finally, it is hypothesized that patients who receive SCP care are more adequately referred to other health care services when they have high distress levels compared to those who receive usual care.

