*Satisfaction with care *will be measured with the EORTC IN-PATSAT32 [25]. This questionnaire was designed to assess cancer patients' perception of the quality of medical care, nursing care and care organization and services received in the hospital. The EORTC IN-PATSAT32 contains 11 multi-item and 3 single-item scales. These include the doctors' technical skills, interpersonal skills, information provision, and availability; the nurses' technical skills, interpersonal skills, information provision, and availability; the other hospital staff's interpersonal skills and information provision scale; the exchange of information single-item scale; the waiting time; the hospital access; the comfort single-item scale; and the general satisfaction single-item scale.

*Illness perception *will be measured using the Brief Illness Perception Questionnaire (B-IPQ) [26]. The scale has 9 items, measuring (a) cognitive representations (consequences, timeline, personal control, treatment control, identity); (b) emotional representations (concern, emotion); (c) illness comprehensibility; and (d) an open-ended response item on the 3 most important causal factors of illness.

*Comorbidity at the time of questionnaire completion *will be assessed by the adapted Self-administered Comorbidity Questionnaire (SCQ) [27]. Patients will be asked to identify comorbid conditions developed in the past 12 months. The adapted SCQ lists 14 medical conditions (with the option to list up to 3 additional conditions), and assesses if the patient is treated for the comorbid condition and the perceived impact on the patients' functioning.

*Anxiety and depression *will be assessed using the Hospital Anxiety and Depression Scale (HADS) [28]. The HADS has 14-items, with 7 items each for anxiety and depression. Each item is scored from 0 to 3, where a score of 3 represents a state corresponding to the worst anxiety or depression. The sum of these items produces two subscales ranging from 0 to 21. A score of 8 will be used as a cut-off value for both depression and anxiety [28].

*Physical and mental fatigue *will be measured using the Fatigue Assessment Scale (FAS) [29], which consists of 10-items with 5 items each reflecting physical and mental fatigue. The items are scored on a 5-point response scale ranging from 1 (never) to 5 (always).

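### Five care-arm interactions are tested on the outcome measures under a blanket p<0.05 rule with no error control across them, and the sentence that plans them announces three modifiers but enters five

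*Protocol article*

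**What the plan says.** Three statements in the protocol article bear on this.

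- **Objectives and hypotheses** raises the possibility of harm in some patients: "there may be subgroups (dependent on patient characteristics, such as age, education, and personality) that will be influenced in a negative way".
- **Statistical analysis** turns this into a plan in one sentence. Its first half reads "Differential effects of SCP care by age, type of cancer and baseline levels of the outcomes of interest will be assessed for the outcome measures", which names three modifiers. Its second half says this is done "by adding terms for the interaction between age, educational level, personality, type of cancer and baseline levels and care arm to the regression models", which names five. Educational level and personality appear only in the second half.
- **Statistical analysis** also sets one rule for every test: "All statistical tests will be two-sided and considered significant if *p*<0.05".

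The outcomes are numerous. "Primary outcomes include patients' satisfaction with information provision, and satisfaction with care"; the secondary list adds quality of life, illness perception, health care use and distress. The interaction sentence does not use the division into primary and secondary outcomes. The article does not call the interactions exploratory, rank them or adjust for their number.

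**The concern.** Testing interactions formally, with the modifiers named beforehand, is sound. The weakness is that five such tests per outcome fall under the same significance rule as the main comparison. By the article's own rule, any one of them that falls below 0.05 may be called significant.

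A statement that the SCP works differently by age, education or personality could influence who is offered one. The Discussion says the results may be used to persuade care providers and insurers. A subgroup finding should therefore carry a label that shows how much evidence stands behind it.

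The three-versus-five mismatch adds to this. A reader cannot tell from the sentence whether effects by educational level and personality are part of the declared assessment or only terms in the model.

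**Working it through.** **Inputs from the article**
- Modifiers entered: 5 (Statistical analysis).
- Significance level: 0.05, two-sided, for all tests (Statistical analysis).
- Primary constructs: 2 (Objectives and hypotheses).
- Scores in the two primary instruments (Patient reported outcomes): the INFO26 is listed with 4 scales and 6 single items, so 10. For the other, "The EORTC IN-PATSAT32 contains 11 multi-item and 3 single-item scales", so 14. Total 24.
- Analysable patients: about 300 (Sample size).

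**Assumptions, not in the article**
- The SCP effect is uniform, so every interaction is null.
- The five modifiers are independent of each other.
- Test statistics for different outcomes are equally correlated, at 0.5 with a range of 0.3 to 0.8.
- There is one test per modifier and outcome, at one time point.

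**The plan's own figures.** The article gives no error rate for the set of interactions; 0.05 per test is its only figure for them. Its power of 0.98 for a 0.5 SD main effect is roughly reproduced. The standard error is √(4/300) = 0.115, and Φ(0.5/0.115 − 1.96) = 0.991 without clustering. With 12 hospitals and an assumed intracluster correlation of 0.01, the design effect is 1 + 24 × 0.01 = 1.24 and the power is 0.973.

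**One outcome.** 1 − (1 − 0.05)^5 = 1 − 0.774 = 0.226, about 4.5 times 0.05. If the five test statistics are themselves correlated at 0.2, 0.3 or 0.5, this falls to 0.22, 0.21 or 0.18.

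**Several outcomes.** Let f be the chance that one modifier gives at least one p<0.05 over the outcomes tested. Over five independent modifiers the chance is 1 − (1 − f)^5. For two outcomes correlated 0.5, f = 0.091, so 1 − 0.909^5 = 0.38. For 24 scores correlated 0.5, f = 0.458, so 1 − 0.542^5 = 0.95.

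| Outcomes tested | Interaction tests | Independent | Correlation 0.3 | 0.5 | 0.8 |
|---|---|---|---|---|---|
| 1 | 5 | 0.23 | 0.23 | 0.23 | 0.23 |
| 2 | 10 | 0.40 | 0.39 | 0.38 | 0.33 |
| 6 | 30 | 0.79 | 0.75 | 0.69 | 0.53 |
| 24 | 120 | 0.998 | 0.99 | 0.95 | 0.74 |

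**Where the chance passes one half.** With independent tests, ln 0.5 / ln 0.95 = 13.5, so 14 tests are needed, which is reached at the third outcome (15 tests, 0.54). With correlation 0.5 it takes four outcomes (0.57). With correlation 0.9, outside the range above, six outcomes give 0.44 and 24 give 0.59.

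**Power for a true interaction.** For a binary modifier with share p in one category and 300 patients without clustering, SE = √(4/(300p) + 4/(300(1 − p))). For a 0.5 SD interaction the power, Φ(0.5/SE − 1.96), is:
- p = 0.5: SE 0.231, power 0.58
- p = 0.3: SE 0.252, power 0.51
- p = 0.2: SE 0.289, power 0.41

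The article adjusts for the baseline value of the outcome. If baseline and follow-up correlate 0.5 (an assumption), each SE shrinks by √(1 − 0.25) = 0.866, and the powers become about 0.70, 0.63 and 0.52.

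**The case against.** The best defence is that this is a condensed article. The status and ranking of subgroup analyses are commonly settled in a full protocol or analysis plan, which is not shown, and their absence alone is no fault. That stands as far as silence goes. It does not answer the point fully, because the article is not silent: it sets p<0.05 for all tests, and its list of modifiers is inconsistent within one sentence. A later plan that used an adjusted threshold would depart from the published rule.

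Several stronger readings are tempting, and the article does not support them.

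- **That a false subgroup claim is likely whatever is tested.** It is not for one outcome (0.23) or for two (about 0.38). Figures near certainty require every scale of both instruments to be tested against every modifier. The article describes the scales but does not say that. It does speak of the outcome measures in general, so more than two outcomes is a fair reading; how many is unknown.
- **That these rates measure false claims of harm.** They count any significant interaction, in either direction. An interaction may mean only a smaller benefit in one group. The article also judges clinical importance separately, at about 0.5 SD.
- **That a true interaction is likely to be missed.** Power for a 0.5 SD interaction exceeds one half in two of the three unadjusted cases above, and in all three with a baseline correlation of 0.5. The Sample size section also considers each tumour type separately (150 patients, power 0.83), although that is power within a type and not power for an interaction.
- **That the Objectives contradict the analysis section.** The Objectives list is tentative and given as examples, so it need not match. The real mismatch lies between the two halves of the analysis sentence.

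**Conclusion.** The point holds, at minor severity. The article places five care-arm interactions per outcome under a blanket p<0.05 rule without control across them. Under a uniform SCP effect this gives a 0.23 chance of at least one falsely significant interaction for one outcome, and about 0.38 (0.33 to 0.39) for two. The chance exceeds one half only when several outcomes or scales are each tested, and reaches 0.74 to 0.99 for all 24 primary-instrument scores. These figures assume independent modifiers, outcome correlations of 0.3 to 0.8 and one test per modifier and outcome. Correlated modifiers would lower them; added time points or secondary outcomes would raise them.

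The three-versus-five mismatch is a plain drafting inconsistency and needs no assumption.

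**What to change.** In the Statistical analysis section:

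1. Use one list of modifiers in both halves of the interaction sentence.
2. Declare the care-arm interactions exploratory and exempt them from the blanket p<0.05 rule.
3. Report each interaction as an estimate with a 95% CI.
4. State that no conclusion of subgroup benefit or harm will be drawn from a nominal p<0.05 alone.

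This changes wording only; no patients, data or procedures are affected. The price is that a nominal subgroup result cannot be presented as established. A confirmatory test of a few modifiers on one named outcome, with adjustment, is a possible alternative, but it is a choice for the trial team and is not needed to resolve the point.
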